**Proprietary and Confidential**

# SCHEMA

Histologic Diagnosis of Relapsed or Refractory Small Cell Lung Cancer (SCLC) Post-1st line chemotherapy

Response/Stable Disease/Clinical Benefit

Continue until clear disease progression.

Informed consent

Treatment with 2 cycles of CPI-613

Cycle length: 4 weeks

Treatment given on days 1 and 4 of weeks 1 through 3

Radiographic surveillance

Scan performed during week 4 of cycle 2, 4, 6 and every 2 cycles thereafter

No Response

Discontinue treatment

**Primary Objective**

To evaluate the response rate (RR) of CPI-613 in patients with relapsed or refractory SCLC who have failed 1st chemotherapy.

**Secondary Objective**

To evaluate the safety, toxicity, progression-free-survival (PFS) and overall survival (OS) of CPI-613 in these patients.

**Primary objective**

To evaluate the safety and anti-cancer activities (assessed based on Response Rate) of CPI-613 in patients with advanced unresectable bile duct cancer who have failed available therapies.

**Secondary Outcome measures**

- Progression-free survival
- Overall Survival

**Design**

Open-label single arm

* Maximum number of cycles allowed is 6

** Two additional cycles will not be given if the patient no longer meets eligibility criteria, has worsening of biliary function, or has symptomatic progression.

Table of Contents

[SCHEMA 3](#_Toc363723897)

[1.0 BACKGROUND AND STUDY OBJECTIVES 6](#_Toc363723898)

[1.1 Small Cell Lung Carcinoma 6](#_Toc363723899)

[1.2 CPI-613 6](#_Toc363723900)

[2.0 STUDY DESIGN 7](#_Toc363723901)

[2.1 Study Objective 7](#_Toc363723902)

[2.2 Outcome Measures 7](#_Toc363723903)

[2.3 Open-Label, Single-Arm Study Design 7](#_Toc363723904)

[3.0 PATIENT ELIGIBILITY CRITERIA 8](#_Toc363723905)

[3.1 Inclusion Criteria 8](#_Toc363723906)

[3.2 Exclusion Criteria 8](#_Toc363723907)

[3.3 Inclusion of Women and Minorities 9](#_Toc363723908)

[4.0 REGISTRATION PROCEDURES 9](#_Toc363723909)

[5.0 STUDY PROCEDURES 11](#_Toc363723910)

[5.1 Pre-Study Screening Tests and Safety Assessment 12](#_Toc363723911)

[5.1.1 Pre-Study Screening Tests 12](#_Toc363723912)

[5.1.2 Safety Assessment 12](#_Toc363723913)

[5.1.3 Tumor Assessment 12](#_Toc363723914)

[5.2 Specifics of Tests Performed During the Study 13](#_Toc363723915)

[5.2.1 ECOG Performance Status 13](#_Toc363723916)

[5.2.2 Clinical Chemistry and Hematology 14](#_Toc363723917)

[6.0 TREATMENT WITH CPI-613 14](#_Toc363723918)

[6.1 Sample Size, Dose Levels and Justification of the Dose 15](#_Toc363723919)

[6.2 Adverse Event-Related Dosing Delay and Dose Modification 15](#_Toc363723920)

[6.3 Duration of Treatment for Each Patient at Each Cohort 16](#_Toc363723921)

[7.0 STUDY DRUG - CPI-613 17](#_Toc363723922)

[7.1 Description of CPI-613 Drug Product 17](#_Toc363723923)

[7.2 Handling of CPI-613 17](#_Toc363723924)

[7.3 Storage of CPI-613 17](#_Toc363723925)

[7.4 Intravenous (IV) Infusion Sets, Syringes and IV Bags to be used for Administration of CPI-613 17](#_Toc363723926)

[7.5 Reconstitution and Administration of CPI-613 18](#_Toc363723927)

[7.6 Request for CPI-613 19](#_Toc363723928)

[7.7 Procurement of Investigational Drug 20](#_Toc363723929)

[7.8 Disposal of CPI-613 20](#_Toc363723930)

[7.9 Calculation of the Amount of CPI-613 for Each Patient 21](#_Toc363723931)

[7.10 Concomitant Medications and Prophylactic Treatment 21](#_Toc363723932)

[8.0 ADVERSE EVENTS LIST AND REPORTING REQUIREMENTS 22](#_Toc363723933)

[8.1 Adverse Event Characteristics 22](#_Toc363723934)

[8.2 STRC SAE Reporting Requirements 23](#_Toc363723935)

# 1.0 BACKGROUND AND STUDY OBJECTIVES

## 1.1 Small Cell Lung Carcinoma

SCLC accounts for ~15% of all lung cancers. SCLC is a common lung malignancy caused by tobacco smoking. There are ~30,000 cases in the US each year. Two-thirds of patients present with extensive stage disease at the time of diagnosis. In patients with extensive stage disease, chemotherapy with a traditional platinum doublet can achieve response rates of up to 80% and improve survival. However, there are few durable responses, and in the majority of these patients, disease eventually returns. Most patients relapse with relatively resistant disease and have a median survival of only 4 to 5 months, and have increased morbidity. Current guidelines from the National Comprehensive Cancer Network (NCCN) recommend clinical trials for patients with recurrent disease (http://www.nccn.org/index.asp).

## 1.2 CPI-613

CPI-613 is a novel anti-cancer agent (Zachar et al. 2011). CPI-613 selectively targets the altered form of mitochondrial energy metabolism in tumor cells, causing changes in mitochondrial enzyme activities and redox status, which leads to apoptosis, necrosis and autophagy of tumor cells (Zachar et al. 2011). The activities of CPI-613 involve the catalytic and regulatory functions of the altered form of the pyruvate dehydrogenase complex (PDC) and the α-ketoglutarate dehydrogenase complex (KGDHC) found in tumor cells (Zachar et al. 2011). Due to its novel mechanism of action and the multi-molecular targeting approach, CPI-613 is equally effective against multi-drug resistance (MDR) cancer cell lines when compared to the parental untreated cancer cell lines, according to *in vitro* studies (Zachar et al. 2011).

According to Phase I dose-escalation trials in patients with various advanced stages of solid and hematologic malignancies, CPI-613 is well-tolerated at doses up to 3,000 mg/m^2^ when infused intravenously over two hours. CPI-613 also exhibits anti-tumor activities in these patients (Pardee et al, 2011a and b, & 2012; Lee et al. 2011 & 2012; Senzer et al 2012), even in the Phase 1 patient population were those with relapsed or refractory disease.

# 2.0 STUDY DESIGN

## 2.1 Study Objective

The objective of this study is to evaluate the safety and anti-cancer activities in patients with relapsed or refractory SCLC who have failed 1 or 2 lines of chemotherapy.

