# 3.0 PATIENT ELIGIBILITY CRITERIA

## 3.1 Inclusion Criteria

Patients must meet all of the following inclusion criteria before enrollment:

A. Histologically or cytologically proven SCLC that has relapsed or been refractory after at least one line of chemotherapy.

B. ECOG Performance Status of ≤2.

C. Must be ≥18 years of age.

D. Expected survival >1 month.

E. No acute toxicities from previous treatment higher than grade 1 at the start of treatment with CPI-613.

F. Women of child-bearing potential (i.e., women who are pre-menopausal or not surgically sterile) must use accepted contraceptive methods (abstinence, intrauterine device [IUD], oral contraceptive or double barrier device) during the study, and must have a negative serum or urine pregnancy test within 1 week prior to treatment initiation.

G. Men must practice effective contraceptive methods during the study, unless documentation of infertility exists.

H. Laboratory values ≤2 weeks prior to registration must be:

- platelet count ≥100,000 cells/mm^3^ or ≥100 bil/L
- absolute neutrophil count [ANC] ≥1500 cells/mm^3^ or ≥1.5 bil/L
- aspartate aminotransferase [AST/SGOT] ≤3x upper normal limit [UNL]
- bilirubin ≤1.5x UNL
- serum creatinine ≤1.5 mg/dL or 133 µmol/L
- albumin >3.0 g/dL or >30 g/L.

I. Mentally competent, ability to understand and willingness to sign an IRB-approved written informed consent form.

J Have access via central line (e.g., portacath) – double lumen due to CPI-613 administration requirements

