## 3.2 Exclusion Criteria

Patients with the following characteristics are excluded:

A. Patients receiving any other standard or investigational treatment for their cancer, or any investigational agent for any non-cancer indication within the past 2 weeks prior to initiation of CPI-613 treatment.

B. Serious medical illness that would potentially increase patients’ risk for toxicity.

C. Any active uncontrolled bleeding or bleeding diathesis.

D. Pregnant women, women of child-bearing potential not using reliable means of contraception, or lactating women.

E. Men unwilling to practice contraceptive methods during the study period.

F. Life expectancy less than 1 month.

G. Treatment with any anti-cancer therapy within the 2 weeks prior to treatment with CPI-613.

H. Patients with untreated central nervous system (CNS) or epidural tumor.

I. Any condition or abnormality which may, in the opinion of the investigator, compromise his or her safety.

J. Unwilling or unable to follow protocol requirements.

K. Active heart disease including myocardial infarction within previous 6 months, symptomatic coronary artery disease, arrhythmias not controlled with medication, or symptomatic congestive heart failure.

N. Evidence of active infection or serious infection (e.g., septic shock with multi-organ dysfunction) within the past month.

O. Patients with known HIV infection.

P. Requirement for immediate palliative treatment of any kind including surgery.

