| * Cycle Length is 4 weeks, with treatment on Days 1 and 4 of Weeks 1 through 3; week 4 is a rest  week (no treatment)  ** The only pre-study data that will be used for data analyses are ECOG status, baseline CT or PET/CT, and LDH. See section 5.1.4 for details.  a: Pre-study requirements must be completed **within** **the following time**  **frames:**  Within **4** weeks: tumor assessments based on contrast CT of chest and abdomen or PET/CT;  Within **2** weeks: medical history, physical exam, vital signs, height, weight, ECOG, evaluation of symptoms and medications, clinical chemistry, hematology, LDH  Within **1** week: pregnancy test for women of childbearing potential  b: Specific chemistries are listed in section 5.2.2. Renal function will be assessed using the Cockcroft-Gault formula.  c: Serum pregnancy test for women of childbearing potential  d: These tests are performed with results available for review within 24 hours before administration of CPI-613  e: CPI-613 is given as a 2-hr IV infusion via a central venous catheter. Treatment with CPI-613 may be adjusted +/- 1 day.  f: Imaging performed while on treatment should be preferably obtained on day 3, 4, or 5 of week 4 during cycles 2, 4,  6 and every two cycles thereafter until progression.  g: Survival and post-study cancer treatment will be monitored bimonthly via telephone contact by the study PA after  patients are taken off of the trial. Phone contact will continue indefinitely.  h: Physical exam and clinical evaluation to be completed within 72 hours prior to treatment with CPI-613 | | | | | | | | | |

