| 🞎 | 🞎 | 🞎 | 1. If the patient is a fertile man, does he agree to practice effective contraceptive methods during the study, unless documentation of infertility exists? |  |
| 🞎 | 🞎 | 🞎 | 1. Does the patient have documentation of the following laboratory values?  - platelet count ≥100,000 cells/mm^3^ or ≥100 bil/L - absolute neutrophil count [ANC] ≥1,500 cells/mm^3^ or ≥1.5 bil/L - aspartate aminotransferase [AST/SGOT] ≤3x upper normal limit [UNL] - bilirubin ≤1.5x UNL - serum creatinine ≤1.5 mg/dL or 133 µmol/L - Albumin >3.0 g/dL or >30 g/L. |  |
| 🞎 | 🞎 | 🞎 | 1. Is the patient mentally competent, able to understand and willing to sign an IRB-approved written informed consent document? |  |
| 🞎 | 🞎 | 🞎 | 1. Does the patient have access via a double lumen central line (e.g., portacath)? |  |
|  | | | | |
| **Yes** | **No** | **N/A** | Exclusion Criteria (All responses must be **NO** in order to enter study) | **Eligibility Confirmation (registrar)** |
| 🞎 | 🞎 | 🞎 | 1. Is the patient receiving any other standard or investigational treatment for their cancer, or have they received any other investigational agent for any indication within the past 2 weeks prior to initiation of CPI-613 treatment? |  |
| 🞎 | 🞎 | 🞎 | 1. Does the patient have a serious medical illness that would potentially increase his or her risk for toxicity? |  |
|  |  |  | 1. Does the patient have any active uncontrolled bleeding or bleeding diathesis? |  |
| 🞎 | 🞎 | 🞎 | 1. Is the patient a pregnant woman, or a woman of child-bearing potential who is not using reliable means of contraception? |  |
| 🞎 | 🞎 | 🞎 | 1. Is the patient a lactating female? |  |
| 🞎 | 🞎 | 🞎 | 1. Is the patient a fertile man who is unwilling to practice contraceptive methods during the study period? |  |
| 🞎 | 🞎 | 🞎 | 1. Is the patient’s life expectancy less than 1 month? |  |
| 🞎 | 🞎 | 🞎 | 1. Has the patient received treatment with any anti-cancer therapy within the 2 weeks prior to treatment with CPI-613? |  |
| 🞎 | 🞎 | 🞎 | 1. Does the patient have an unrelated central nervous system (CNS) or epidural tumor? |  |
| 🞎 | 🞎 | 🞎 | 1. Does the patient have any condition or abnormality which may, in the opinion of the investigator, compromise his or her safety? |  |
| 🞎 | 🞎 | 🞎 | 1. Is the patient unwilling or unable to follow protocol requirements? |  |

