**CCCWFU # 62113 Eligibility Source Documentation Checklist**

**(to be submitted with Protocol Registration Form)**

| **Source Documents Needed (see eligibility form above for changes)** | | | **✓ or N/A** | |
| --- | --- | --- | --- | --- |
|  | Pathology report confirming histologically or cytologically proven extensive stage SCLC that has relapsed or been refractory after one line of chemotherapy? |  | |  |
|  | Lab report documenting all initial required lab values |  | |  |
|  | Documentation that the patient is free from acute toxic effects from previous treatment superior to grade 1 |  | |  |
|  | Documentation of ECOG performance status of 0, 1, or 2 |  | |  |
|  | Documentation of expected survival > 1 month |  | |  |
|  | Most recent H&P documenting patient is 18 years of age or older |  | |  |
|  | For female patients of child-bearing potential (i.e., pre-menopausal or not surgically sterile), documentation that the patient agrees to use accepted contraceptive methods (abstinence, intrauterine device [IUD], oral contraceptive or double barrier device) during the study, and agrees to have a negative serum or urine pregnancy test within 1 week prior to treatment initiation. |  | |  |
|  | For male patients, documentation of infertility OR for fertile men, documentation that patient agrees to practice effective contraceptive methods during the study |  | |  |
|  | Lab report performed (< 2 weeks) documenting the following values:   - Platelet count ≥100,000 cells/mm^3^ or ≥100 bil/L - Absolute neutrophil count ≥1500 cells/mm^3^ or ≥1.5 bil/L - Aspartate aminotransferase [AST/SGOT] ≤3x upper normal limit [UNL] - Bilirubin ≤1.5x UNL - Serum creatinine ≤1.5 mg/dL or 133 µmol/L - Albumin > 3.0g/dL or 30 g/L |  | |  |
|  | Documentation that the patient is mentally competent, able to understand and willing to sign an IRB-approved written informed consent document |  | |  |
|  | Copy of signed consent form |  | |  |
|  | Documentation that the patient is not receiving any other standard or investigational treatment for their cancer, or has received any other investigational agent for any indication within the past 2 weeks prior to initiation of CPI-613 treatment |  | |  |
|  | Documentation that the patient has not received cancer immunotherapy within the past 2 weeks prior to initiation of CPI-613 treatment |  | |  |

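### The eligibility texts contradict each other on prior lines, stage and CNS tumor, and bile duct wording remains in an SCLC protocol

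*Protocol*

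**What the plan says.** **Disease.** The Schema, the first Primary Objective, Section 2.1 and Section 3.1 all concern SCLC. A second primary objective in the front matter concerns "patients with advanced unresectable bile duct cancer who have failed available therapies". The footnote under Design and the first bullet of Section 6.3 also make worsening biliary function part of the decision on further treatment.

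**Prior therapy.** There are four wordings:
- Primary Objective: "patients with relapsed or refractory SCLC who have failed 1st chemotherapy". The Schema likewise places the trial after first-line chemotherapy.
- Section 2.1: "patients with relapsed or refractory SCLC who have failed 1 or 2 lines of chemotherapy".
- Section 3.1 A: "Histologically or cytologically proven SCLC that has relapsed or been refractory after at least one line of chemotherapy". The Eligibility Checklist in Appendix A sets the same minimum, with no maximum.
- Eligibility Source Documentation Checklist in Appendix A: "proven extensive stage SCLC that has relapsed or been refractory after one line of chemotherapy".

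**Stage.** Both Appendix A checklists require extensive stage, and the title of Table 6-1 names it. The Schema, both SCLC objectives and Section 3.1 do not.

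**CNS disease.** Section 3.2 H excludes "Patients with untreated central nervous system (CNS) or epidural tumor". The Eligibility Checklist asks instead: "Does the patient have an unrelated central nervous system (CNS) or epidural tumor". The source-document checklist also has *unrelated*.

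**Use of the population.** Section 2.2 defines the primary outcome as the response rate in the patients just described in Section 2.1. Sections 6.1 and 9.0 plan 20 patients and a descriptive analysis. A footnote to Table 5-1 says: "The only pre-study data that will be used for data analyses are ECOG status, baseline CT or PET/CT, and LDH".

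**The concern.** This is a single-arm pilot whose purpose is a first estimate of response rate. With no comparator, the estimate can be read only against a clear account of who was enrolled. If the objective, the criteria and the forms describe different patients, the result need not refer to the population named in the objective.

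Several of the texts are gates to enrollment. Section 3.1 requires every inclusion criterion to be met before enrollment. The Eligibility Checklist requires every inclusion answer to be yes and every exclusion answer to be no. Section 4.0 refuses registration without the supporting documents, which the source-document checklist lists. Where these differ, the same patient can be accepted by one and refused by another.

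The CNS wording is a safety matter as well. The forms are the registrar's check on the exclusion criteria, and because both carry the same substitution, neither corrects the other.

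**Working it through.** No formula decides this point. The check runs typical patients through each text as written, assuming that they meet every other criterion.

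| Patient | Section 2.1 | Sections 3.1 and 3.2 | Eligibility Checklist | Source-document checklist |
| --- | --- | --- | --- | --- |
| Extensive stage, one prior line | inside | eligible | passes | passes |
| Extensive stage, two prior lines | inside | eligible | passes | not clearly covered |
| Extensive stage, three or more prior lines | **outside** | **eligible** | passes | not clearly covered |
| Limited stage, one prior line | inside | **eligible** | **fails** | **fails** |
| Extensive stage, one prior line, untreated CNS metastases from SCLC | not addressed | **excluded** | **not caught** | **not caught** |

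1. *Three or more prior lines.* Section 3.1 A and the Eligibility Checklist set a minimum of one and no maximum. Section 2.1 stops at two. Such a patient can be enrolled and counted in a response rate that Section 2.2 ties to Section 2.1.
2. *Limited stage.* Section 3.1 A has no stage condition, while both forms do. The patient meets the protocol's criteria and cannot be registered.
3. *Untreated CNS metastases.* Section 3.2 H excludes this patient. A brain metastasis of the lung cancer is not an unrelated tumor, so a truthful answer to the form's question is no, and no is the answer that allows entry. The source-document checklist has the same wording and the same result.
4. *Bile duct text.* Section 3.1 A and both checklists require proven SCLC, so the second objective changes no row of the table. The biliary wording does reach operative text in Section 6.3, where it stands in a rule on duration of treatment.

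**Size.** With 20 patients, each carries 1/20 = 5 percentage points of the response rate.

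**The protocol's own figure.** Section 9.0 states that the two-sided 95% interval extends no more than 0.21 from the observed rate, assuming a rate of 0.5 and n = 20. The normal approximation gives 1.96 × √(0.5 × 0.5 / 20) = 0.219. Wilson gives 0.201, Jeffreys 0.207 and exact limits 0.228, so 0.21 is met at that rate by Wilson and Jeffreys limits. No feature of the population enters this calculation. The conflict affects which patients the interval describes and leaves its width unchanged.

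**The case against.** The strongest reply is that Sections 3.1 and 3.2 already give one explicit, binding list, and that the other passages are objectives, headings or aids to paperwork.

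- Section 2.1 is an objective and enrolls nobody.
- The wording about first chemotherapy can be read as compatible with a minimum of one line.
- The source-document checklist refers the reader back to the eligibility form, which agrees with Section 3.1 A on prior lines.
- A limited-stage patient is stopped at registration, so the stage conflict narrows entry and does not mix stages in the estimate.
- Exclusion 3.2 H still binds the investigator, whatever the form says.

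Much of this stands. A reader might infer that the response rate has no defined population at all; the documents do not support that, because 3.1 and 3.2 define one. A reader might also infer that the bile duct objective makes the result uninterpretable. It cannot, because no bile duct patient can be enrolled.

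The reply does not remove three things. Section 2.1 has an upper limit that 3.1 A lacks, and the primary outcome points to Section 2.1. The forms impose a stage condition that the criteria do not contain. Both forms fail to screen for an exclusion that the protocol states. An investigator's duty under 3.2 H does not make the registrar's check work.

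**Conclusion.** The point holds as a contradiction between eligibility texts, with three concrete consequences: enrollment outside the stated objective (three or more prior lines), refusal of patients whom 3.1 A admits (limited stage), and a safety gap at registration (untreated CNS disease). It rests on reading each text literally. An analysis plan could not repair it once patients have been registered under conflicting rules.

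Three stronger readings are tempting and should not be made:

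- *That patients entering third-line treatment lie outside the objective.* They have failed two lines, which Section 2.1 includes. Only three or more prior lines fall outside.
- *That the conflict moves the response rate by a known amount.* The protocol gives no response rate by number of prior lines or by stage for previously treated patients. Section 1.1 offers only a first-line response of up to 80% in extensive disease and a median survival of 4 to 5 months after relapse. Any figure would rest on assumed rates.
- *That the Table 5-1 footnote forbids describing prior treatment.* It does say *only*, but it refers to Section 5.1.4 for details, and that section lists items to be documented without prohibiting others. Prior treatments are recorded on the Protocol Registration Form. The footnote is worth clarifying, no more.

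Nor does the point call for response rates by subgroup. With 10 patients in a group, the half-width at a rate of 0.5 is 1.96 × √(0.25 / 10) = 0.31, too wide to demand in a 20-patient descriptive pilot.

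**What to change.** 1. The sponsor and the investigator should settle one statement of disease, stage, number of prior lines and CNS exclusion. Which statement is right is theirs to decide. Use it in the Schema, the Primary Objective, Sections 2.1, 3.1 and 3.2, the title of Table 6-1 and both Appendix A checklists.
2. Delete the bile duct objective. Remove the biliary wording from the Design footnote and from Section 6.3. Whether anything replaces it there is a clinical decision for the sponsor and the investigator.
3. Make both Appendix A checklists match Sections 3.1 and 3.2 item by item, including the CNS exclusion. This comparison will also bring up the torsade de pointes item on the source-document checklist, which has no counterpart in Section 3.2.
4. Optionally, state that the Table 5-1 footnote does not bar descriptive reporting of the prior treatments already collected at registration.

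The cost is one amendment to protocol text and two forms. It needs no new data, no extra patients and no change to the analysis, and it should be made before further patients are registered.
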